### Rationale for study design

We selected a pragmatic type II hybrid effectiveness-implementation study, as it allows simultaneous mixed-methods assessments of intervention effectiveness and implementation strategies in “real life” health systems settings [35, 37]. Through this convergent design [38], we intend to routinely disseminate [39] our research findings to MoH partners. Effectiveness measures will provide evidence as to whether the ICBHSS intervention impacts child mortality and, via this pragmatic design, will provide more generalizable estimates than traditional study designs [35]. Assessing the implementation strategy will generate knowledge about process outcomes and feasibility including barriers and enabling factors, core components which are generalizable and where local adaptation is needed for replication in other settings. This actionable knowledge is a critical need for implementors in low- and middle-income settings, particularly for complex health systems interventions [12, 40].

Although our preliminary Kozah pilot study provided initial data to suggest ICBHSS’s effectiveness, these results have limited capacity to establish causation due to single-arm design and lack of a valid comparison group. Furthermore, our pilot study was not designed to evaluate implementation strategies required to provide generalizable data that could inform replication and scale activities.

To address these limitations and rigorously assess ICBHSS effectiveness and implementation strategy, we will conduct a summative mixed-methods evaluation using a modified RE-AIM (reach, effectiveness, adoption, implementation, maintenance) framework [42]. This framework is a practical tool that assesses complex interventions in real-world practice including measures of clinical effectiveness and implementation strategy [43]. Effectiveness will be measured using the primary outcome, under-five child mortality, utilizing a stepped-wedge cluster randomized control design. Implementation strategy will be assessed by measures of reach, adoption, implementation, and maintenance of the ICBHSS intervention through data collection with key informants, facility, and the general catchment populations [44]. This adapted evaluation framework will enhance traditional stepped-wedge design by including measures of implementation fidelity [45].

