#### Stepped-wedge cluster randomized control trial

This pragmatic design leverages the sequential or staggered rollout of the ICBHSS model and will facilitate an assessment of effectiveness as well as implementation strategy through coverage and adoption metrics by comparing geographically organized clusters [50, 51]. It includes four clusters that organize intervention health facilities by district: Bassar, Binah, Dankpen, and Kéran. The ICBHSS cluster initiation order will be randomized annually with four steps, as it was independently determined by the IH programs team that baseline health needs were similar in each cluster. Community-based household surveys adapted from Demographic and Health Survey (DHS) modules previously implemented in Togo [3] and focusing on demographic, maternal, and child health data will be conducted in each cluster at baseline, 12, 24, 36, and 48 months.

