### Data collection and analysis

All metrics will be organized using a modified RE-AIM (reach, effectiveness, adoption, implementation, maintenance) framework [56]. Table 4 summarizes data collection and analysis plans organized by primary aim and adapted RE-AIM domains.

**Table 4 Tab4:** Summary of key study measures organized by aim and domain using modified RE-AIM evaluation framework

Study aim	RE-AIM framework domain	Outcome(s)/indicator(s)	Data source	Indicator definition/clarification
Study aim I: implementation strategy	Reach	*Health service coverage*		
		CHW home visits	Community-based household survey	Proportion of participants in the last year reporting a home visit by an IH CHW.
		CHW home treatment	Community-based household survey	Proportion of participants in the last year reporting treatment at home by an IH CHW
		Health facility treatment	Community-based household survey	Proportion of participants in the last year reporting care at a health facility.
		*Early service access for child health*		
		Malaria coverage	Community-based household survey	Proportion of children under five reported febrile receiving guideline-based treatment within 24 h of symptom onset.
		Pneumonia coverage	Community-based household survey	Proportion of children under five with a cough and proportion of those receiving guideline-based treatment within 24 h of symptom onset.
		Gastrointestinal illness coverage	Community-based household survey	Proportion of children under five with diarrhea receiving guideline-based treatment within 24 h of symptom onset.
		Malnutrition coverage	Community-based household survey	Proportion of children under five with malnutrition receiving effective treatment.
		Coverage estimate of prenatal care	Community-based household survey	Proportion of pregnant women in the last two years who completed four ANC visits.
		Percentage of births at healthcare facility	Community-based household survey	Proportion of pregnant women in the last two years who delivered in a health facility
		Percentage of births at home	*Community-based household survey*	Proportion of pregnant women who delivered at home in last 2 years.
		Coverage estimate of post-natal care	Community-based household survey	Proportion of post-partum women who received post-natal care in last 2 years.
Study aim 2: effectiveness	Effectiveness	*Primary outcome*		

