		Children under five mortality rate	Community-based household survey	Using a standard birth/death history table, calculate under-five mortality rates, and compare risk of death before age five across surveys with the Cox proportional hazards regression using survey year as the explanatory variable. Children still alive and under age five at the time of survey will be right censored.
		*Secondary outcomes*		
		Neonatal mortality rate	Community-based household survey	The neonatal mortality rates from all births reported by respondents in the 5 years prior to the survey using the same methods described for under-five mortality, adjusted for 28 days.
		Children under one mortality rate	Community-based household survey	The under-one mortality rates from all births reported by respondents in the 5 years prior to the survey using the same methods described for under-five, adjusted for 1 year.
		Children under two mortality rate	Community-based household survey	The under-two mortality rates from all births reported by respondents in the 5 years prior to the survey using the same methods described for under-five, adjusted for 2 years.
		Maternal mortality rate	Community-based household survey	Exploratory maternal mortality analysis based on the sisterhood reports [57, 58].
		Quality of care parameters		
		Timeliness/promptitude of child care for malaria	Routine programmatic data	Proportion of children under five reported febrile and the proportion who received effective antimalarial treatment within 24 h of symptom onset.
		Timeliness/promptitude of child care for pneumonia	Routine programmatic data	Proportion of children under five reported with cough and the proportion of those children who received an effective pneumonia treatment within 24 h of symptom onset.
		Timeliness/promptitude of child care for diarrhea	Routine programmatic data	Proportion of children under five reported with diarrhea and the proportion of those children who received an effective treatment for diarrheal disease within 24 h of symptom onset.
		CHW technical competence	Routine programmatic data	Proportion of IH CHWs who adhere to evidence-based protocols for iCCM and maternal health.
		Facility clinical staff technical competence	Routine programmatic data	Proportion of facility clinical staff who adhere to evidence-based protocols for iCCM and maternal health.

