#### Primary aim 1: effectiveness

##### Effectiveness

We define *effectiveness* metrics as those that assess the impact of the ICBHSS initiative using annual community household surveys, routine programmatic data, and the health facility assessments. The community-level primary outcome by district uses under-five mortality rates as well as the secondary outcomes of neonatal, under-one, under-two, and maternal mortality rates. We will additionally evaluate quality of care parameters focusing on timeliness of child healthcare through promptitude of treatment reception following illness diagnosis and health facility readiness scores. Lastly, we will assess equity through secondary analyses of under-five mortality by household wealth quintiles, maternal education levels, and distance from the nearest health facility.

*Primary outcome: under-five mortality rates*. We will calculate under-five mortality rates from all births reported by respondents using a standard birth/death history table. We will calculate under-five mortality rates and compare the risk of death before age five across surveys with the Cox proportional hazards regression using intervention exposure as the explanatory variable. Children still alive and under age five at the time of survey will be right censored.

*Secondary outcomes: neonatal, under-one, and under-two mortality rates*. We will calculate the neonatal, under-one, and under-two mortality rates from all births reported by respondents using the same methods described above adjusted for 28 days, 1 year, and 2 years.

*Secondary outcome: maternal mortality*. We will calculate an exploratory maternal mortality analysis based on sisterhood reports [57, 58].

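### Table 4 fits the primary Cox model on survey year, while the text fits it on intervention exposure; the survey-year version does not estimate the programme's effect

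*Protocol article*

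**What the plan says.** The section Data collection and analysis states that "Table 4 summarizes data collection and analysis plans organized by primary aim and adapted RE-AIM domains", so the table restates the plan and does not add a separate analysis. Its primary-outcome row says the study will "compare risk of death before age five across surveys with the Cox proportional hazards regression using survey year as the explanatory variable".

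The text under Primary aim 1: effectiveness covers the same outcome, with the same birth and death histories and the same right-censoring rule. There the study will "compare the risk of death before age five across surveys with the Cox proportional hazards regression using intervention exposure as the explanatory variable".

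On design, the Rationale says: "Effectiveness will be measured using the primary outcome, under-five child mortality, utilizing a stepped-wedge cluster randomized control design". The stepped-wedge section adds: "It includes four clusters that organize intervention health facilities by district: Bassar, Binah, Dankpen, and Kéran", and "The ICBHSS cluster initiation order will be randomized annually with four steps". Every district is surveyed at baseline, 12, 24, 36 and 48 months, and a new district starts every 12 months. Of the single-arm pilot, the Rationale says that "these results have limited capacity to establish causation due to single-arm design and lack of a valid comparison group".

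**The concern.** The two sentences are nearly the same but name different explanatory variables, and so different estimands. The exposure coefficient contrasts child-time under the programme with child-time without it. The survey-year coefficient is the change in the hazard of death from one survey round to the next, pooled over districts whether or not they have started.

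A model containing only survey year gives the same answer whichever order the districts were randomised in. It repeats the before-after comparison that the protocol considers too weak in the pilot. The Discussion names temporal trends as a threat and cites the analysis plan as part of the mitigation; under the Table 4 wording the trend itself becomes part of the estimate. The neonatal, under-one and under-two rows of Table 4 borrow the under-five method, so the conflict carries into them.

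**Working it through.** No figure in the plan needs reproducing; the contradiction is textual. The calculation shows what each wording would estimate.

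**Inputs from the protocol.** Four districts; one new district every 12 months; surveys at 0, 12, 24, 36 and 48 months; baseline under-five mortality 70 per 1000; target reduction 30%, taken as a hazard ratio (HR) of 0.70.

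**Assumptions.** Rollout at months 0, 12, 24 and 36 (the timeline in Table 2 is not legible in the copy reviewed). Deaths per 1000: 25 neonatal, 20 at 1–11 months, the rest at 12–59 months. Background decline 0%, 2% or 4% a year. Birth-history window 1 to 15 years: the primary outcome has no stated window, and the 5-year limit appears only in secondary-outcome rows. Expected deaths and child-time were fitted with a piecewise-exponential model by age, as a stand-in for Cox.

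**1. Survey year only, no true effect.** With the same look-back at each survey, the apparent HR over 48 months at annual decline r is (1 − r)^4.
- r = 2%: 0.98^4 = 0.922
- r = 4%: 0.96^4 = 0.849, an apparent reduction of 15%, half of the 30% target

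The fitted model gives the same values.

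**2. Survey year only, true HR 0.70, no trend, no long look-back.** The share p of districts exposed is 0, 1/4, 2/4, 3/4 and 1 at the five surveys. The ratio to baseline is 1 − 0.30p, giving 0.925, 0.85, 0.775 and 0.70. Districts not yet started dilute the 12-, 24- and 36-month contrasts. At 48 months none is untreated and 0.70 is recovered.

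**3. Same truth, linear survey-year term over 48 months, window varied.**

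| Births counted | Survey-year HR over 48 months |
|---|---|
| last 1 year | 0.70 |
| last 5 years | 0.83 |
| last 10 years | 0.92 |
| last 15 years | 0.95 |

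Only the window changes, so the 48-month dilution comes from births and child-time before rollout that are still counted in later surveys.

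**4. Candidate replacements, 5-year window.**
- Exposure on child-time, no time term; no effect, 4% a year decline: HR 0.89 (truth 1.00).
- Exposure on child-time plus survey year; same scenario: about 0.93 (truth 1.00). Survey year does not capture when the child was at risk.
- Exposure set by the district's status at the survey, plus survey and district; true HR 0.70, no trend: 0.95.
- Exposure on child-time plus calendar period of risk plus district: 1.00 when the truth is 1.00, and 0.70 when it is 0.70.

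**The case against.** The best defence is that the document leans clearly one way. Table 4 is a summary, the fuller text names exposure, and the Rationale and the stepped-wedge section tie effectiveness to the randomised rollout. Table 4 also reverses the numbering of the two aims, which suggests drafting residue. An analysis plan that is not shown may settle the matter. This stands as an argument about likelihood: a reader might infer that the trial will be analysed as a plain before-after comparison, and the document does not support that. It does not remove the conflict, because the row defines the only primary outcome and no precedence is stated.

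A reader might also infer that the survey-year model shrinks a true HR of 0.70 to 0.83 over 48 months because untreated districts remain in the later surveys. That does not hold. On the assumed rollout all four districts have started by month 36, and 0.83 appears only with a 5-year birth window, which the document does not state for the primary outcome.

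Finally, one might think that replacing one variable name by the other settles the matter. It removes the contradiction, but step 4 shows that exposure without a suitable time term, or defined by status at survey, can still mislead. The lack of those details in a condensed article is not itself an error; they matter because the sentence has to be rewritten anyway.

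**Conclusion.** The contradiction is explicit and concerns the primary analysis. Read literally, the Table 4 version has no exposure term and ignores the randomised order. With no true effect it returns about 0.92 or 0.85 over 48 months for an assumed background decline of 2% or 4% a year; any non-zero trend is absorbed in the same way, whatever the window. With a true HR of 0.70 and no trend, its result ranges from 0.70 to 0.95 for windows of 1 to 15 years. The trend rates, age pattern of deaths, rollout months and birth window are assumptions. That a survey-year-only model cannot separate programme from trend does not depend on them.

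**What to change.** In the primary-outcome row of Table 4, replace survey year by intervention exposure as the variable whose coefficient is the primary effect, and use the identical sentence under Primary aim 1. In that sentence or the analysis plan:

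- define exposure on child-time, as a time-varying covariate that switches at the rollout date of the child's district;
- adjust for the calendar period in which the child was at risk, not for survey year alone;
- account for district;
- state the birth-history window for the primary outcome.

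The same wording should govern the neonatal, under-one and under-two analyses that refer back to it.

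The cost is one sentence in the table, a short paragraph in the analysis plan, a little more work splitting birth histories by date, and some loss of precision from the time adjustment. No new data are needed.

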2.	Removal of point-of-care costs in IH intervention public sector health facilities *Evidence:* [16–19]	- Pertains to all children under five, pregnant/post-partum women, women of reproductive age for family planning services, and people living with HIV infections who seek care at study sites. - Includes facility-based consultation fees, medications, supplies, and services provided at IH intervention sites and advanced care referrals at the district or regional hospital. - Selected fees and coverage population chosen in consultation with MoH and based on national and global guidelines.
3.	Proactive community-based IMCI using trained, equipped, supervised, and salaried CHWs with additional services including linkage to family planning and counseling, HIV testing, and referrals *Evidence:* [11, 19–27]	- Candidate selection from community by local leadership, health facility, and IH staff. - Preference for female residents who meet selection criteria (some literacy, pre-test/post-test results, demonstrated related competencies). - Pre-service 23-day training in IMCI, maternal health, and HIV counseling and testing led by MoH and IH staff. - In-service 5-day training in family planning and counseling led by MoH and IH staff. - All training materials developed in consultation with MoH and based on national/global guidelines and evidence-based materials from Association Togolaise pour le Bien-Être Familial, Better Birth Project, Last Mile Health, Muso, and Partners In Health. - Equipped with materials (training guides, backpacks, timers, thermometers, scales, MUACs, rapid tests, medical treatment for basic IMCI cases, notebooks, pens). - CWH consultations, referrals, medicines, and materials are provided free of charge. - Supportive supervision with coaching and mentoring by IH supervisor (nurse/medical assistant). - Regular observation of CHW service delivery through routine programmatic data and community feedback. - CHWs receive a regular equitable salary for full-time work through proactive case seeking and follow-up.

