4.	Clinical mentoring and enhanced supervision by a trained peer coach at public sector health facilities *Evidence:* [28–30]	- Onsite pre-service 4-day training in maternal, reproductive, neonatal, and child health and HIV led by IH clinical mentor (nurse/medical assistant) and medical director. - Training materials developed in collaboration with MoH and based on national/global guidelines and evidence-based materials from WHO, American Academy of Pediatrics, Ariadne Labs, Better Birth Project, Last Mile Health, Muso, and Partners In Health. - Weekly facility-based supportive supervision by IH clinical mentors (nurses, midwives, medical assistants) with prior experience in public sector health facilities. - Regular observation of facility staff service delivery through routine programmatic data and community feedback.
5.	Basic infrastructure/equipment improvements and supply chain management training of pharmacy managers *Evidence:* [15, 31–33]	- Formal infrastructure assessment and equipment needs with MoH using WHO’s SARA tool [41]. - Facilitate structural improvements to improve care delivery. - Equip facility with essential medicines and equipment identified by assessment and national health protocols. - Onsite training in supply-chain management practices, including proper storage of medicines, filling of stock cards, and orders based on average monthly input consumption. - Regular supervision and support by IH clinical mentor.

Preliminary results from the ICBHSS implementation pilot in the Kozah district observed a decline in under-five mortality and increased health service utilization for child and maternal health services at all four intervention sites (ClinicalTrials.gov Identifier: NCT03773913). This evaluation was conducted using a repeated, population-representative, cross-sectional household survey. We anticipate results from 48 months of implementation in 2019.

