#### Primary aim 2: implementation strategy

##### Reach

We define *reach* metrics as the proportion of target population that gained access to the ICBHSS initiative services using the annual community household surveys. We will assess the implementation strategy through individual-level ICBHSS participation with community-level (vis-à-vis CHWs) and facility-level health service utilization using health service coverage estimates and early service access for child health. We will use a mixed-effects generalized linear model to compare pre-intervention to post-intervention proportions for each *reach* metric while adjusting for clustering at the facility and district level and time and allowing for district-level estimates to be random effects. Our primary analysis will not include adjustment for individual-level characteristics, as each district will serve as its own control.

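### Two reach metrics and one effectiveness outcome can exist only after rollout, and timeliness of care as an effectiveness outcome is assigned to routine data for which no pre-rollout collection is described

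*Protocol article*

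**What the plan says.** **Reach.** The Reach section says that a mixed-effects generalized linear model will "compare pre-intervention to post-intervention proportions for each" reach metric, adjusting for time and for clustering by facility and district. It names no link function. Table 4 lists 11 reach metrics. The first two are "Proportion of participants in the last year reporting a home visit by an IH CHW" and "Proportion of participants in the last year reporting treatment at home by an IH CHW".

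**Who the IH CHW is.** Table 1 makes these workers component 3 of the intervention: "CHWs receive a regular equitable salary for full-time work through proactive case seeking and follow-up". The context section says that the four study districts are additional to the pilot district.

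**Quality of care.** Table 4 lists, as secondary effectiveness outcomes, timeliness of child care for malaria, pneumonia and diarrhoea, with routine programmatic data as the source. The malaria row reads "Proportion of children under five reported febrile and the proportion who received effective antimalarial treatment within 24 h of symptom onset". Adherence of IH CHWs to protocols is listed in the same block with the same source. The Effectiveness section says that effectiveness metrics measure the impact of the initiative.

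**Where the routine data come from.** Table 1 mentions them within component 3, "Regular observation of CHW service delivery through routine programmatic data and community feedback", and within component 4, "Regular observation of facility staff service delivery through routine programmatic data and community feedback".

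**Start of the interval.** The Effectiveness section describes timeliness as "promptitude of treatment reception following illness diagnosis". Table 4 counts 24 hours from symptom onset.

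**The concern.** A stepped-wedge trial learns about effect by comparing district-periods before rollout with district-periods after it, adjusted for time. An outcome that cannot occur before rollout, or is not measured then, gives nothing to compare. A significant result on such an outcome restates that the programme was delivered, yet in a results table it would sit beside genuine contrasts and look like one of them.

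For timeliness the trial has a usable source, the household survey, but gives the effectiveness role to the other one. If the quality-of-care effectiveness result is reported from programme records, it may describe only contacts that the programme itself recorded, with no concurrent comparison. Two different starting points for the same interval would also let the reported outcome change with the reading chosen.

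**Working it through.** No figure in the protocol is in dispute, so the check is which outcomes can take a value before rollout, plus one numerical check of the model.

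**1. Outcomes by availability before rollout (Tables 1 and 4)**

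| Outcome | Source | Value before rollout |
|---|---|---|
| Home visit by an IH CHW (reach) | Household survey | Zero by construction |
| Home treatment by an IH CHW (reach) | Household survey | Zero by construction |
| Other 9 reach metrics | Household survey | Measurable |
| IH CHW competence (effectiveness) | Routine data | Undefined: no IH CHWs in service |
| Timeliness, 3 illnesses (effectiveness) | Routine data | No collection described |
| Facility staff competence (effectiveness) | Routine data | Staff exist; no collection described |

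So 2 of 11 reach metrics are structural zeros, 1 effectiveness row is undefined, and 4 more effectiveness rows use a source described only inside the intervention. Three of those 4, the timeliness rows, have a survey counterpart. Services delivered by IH CHWs also appear in the women's care cascade under Adoption, where an increase is to be tested, so the same structural zero recurs there.

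**2. What the structural zero does to the model**

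With p0 and p1 the proportions before and after rollout, log OR = ln[p1/(1 − p1)] − ln[p0/(1 − p0)]. As p0 goes to 0 the second term goes to minus infinity, so the log OR has no finite value. On the risk-difference scale, p1 − p0 = p1 − 0 = p1: the estimated effect is simply post-rollout coverage.

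A binomial logit with fixed wave effects was run on 4 districts × 5 surveys. Assumptions not in the protocol: a logit link; one district switching after each of the first four surveys (10 district-surveys before and 10 after); 300 respondents per district-survey; 50% coverage after rollout. The random district effect was left out because it does not remove the separation.

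| Iteration | Log OR | SE |
|---|---|---|
| 5 | 6.2 | 0.3 |
| 10 | 11.2 | 3.9 |
| 15 | 16.2 | 47.2 |
| 20 | 21.2 | 574.5 |
| 25 | 26.2 | 6,906.5 |

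The estimate rises by about 1 per iteration without converging, and the standard error grows with it.

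A few mistaken reports before rollout would make the estimate finite but not meaningful. With p1 = 0.5 the first term is 0. At p0 = 1/1,000 the log OR is ln(999) = 6.9; at p0 = 1/10,000 it is ln(9,999) = 9.2. Reporting error would set its size.

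**3. The timeliness rows against their survey counterparts**

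Table 4 also contains, under Reach, survey indicators of guideline-based treatment inside 24 hours for fever, cough and diarrhoea. The stepped-wedge section schedules the survey in each cluster at baseline and at 12, 24, 36 and 48 months, giving 4 × 5 = 20 district-surveys. Under the switching assumption above, 10 of these precede rollout. The survey indicators therefore have control-period data and the pre/post model already applies to them. They differ from the effectiveness rows mainly in the treatment wording (guideline-based against effective) and in the RE-AIM label.

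**4. Start of the interval**

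The three timeliness rows and the three matching survey rows in Table 4 all use symptom onset. Only the Effectiveness text uses diagnosis. A child diagnosed two days after symptoms began and treated at once is prompt under the text and late under the table.

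**The case against.** The best defence has four parts.

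- **No pre/post model is stated for the quality-of-care rows.** This is correct. The model is stated for reach and extended to adoption. For quality of care, the protocol speaks only of evaluation and, under the study aims, of longitudinal change. A reader might infer that a planned pre/post test fails for the malaria row; the document plans no such test.
- **Absence of routine data before rollout is not stated.** Also correct. A reader might infer that untreated districts yield no routine data at all. Table 1 supports only the weaker statement that no pre-rollout collection is described. The Maintenance section speaks of programme data at community and facility level, and Table 3 draws on ministry reports for three of the four districts. Neither shows that 24-hour timeliness was recorded before rollout, nor rules it out.
- **The controlled timeliness estimate will be produced anyway, under reach.** This stands, and it limits the consequence. It does not explain why the outcome labelled as effectiveness is tied to the source without a described comparison.
- **The model is not bound to a logit link, and reach is meant to measure access.** Both true. It would be too strong to say that the IH CHW metrics cannot be modelled at all. But under another link the contrast from zero is known before any data are collected. Coverage with an interval serves the purpose of a reach metric; a test does not.

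**Conclusion.** The point holds in limited form. It is firm for three rows: the two IH CHW reach metrics, where the protocol itself prescribes the pre/post model, and IH CHW competence, which cannot show effectiveness because it has no pre-rollout value. For the three timeliness outcomes the finding is a mismatch between label and source: they are called effectiveness, but rest on data described only as part of the intervention, while a better source is already collected and modelled under another heading. The diagnosis/symptom-onset discrepancy is a real but minor contradiction.

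The non-convergence result assumes a logit link. The conclusion that the test is uninformative does not. That pre-rollout IH CHW contact is zero rests on these workers being a component of the intervention and on the study districts being new to the programme. The primary outcome is not touched, nor are the other nine reach metrics. The change should be made, but the trial's main conclusion does not depend on it.

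**What to change.** 1. Take the two IH CHW reach metrics out of the pre/post model. Report them by time since rollout with confidence intervals. Treat the IH CHW element of the adoption cascade in the same way.
2. If a pre/post contrast on CHW contact is wanted, use contact with any CHW. The child-care cascade in Table 4 already refers to care sought from a CHW without restricting it to IH. This helps only if other CHWs were active before rollout, which the protocol does not quantify.
3. Move IH CHW competence and routine-data timeliness to fidelity and report them descriptively.
4. Name the household-survey 24-hour indicators as the source for the three timeliness effectiveness outcomes, with one treatment definition, and analyse them with the model already given in the Reach section.
5. Reconcile the start of the interval between the Effectiveness text and Table 4. Aligning the text with the table is the smaller edit, as all six related rows agree.
6. State whether routine data, including facility staff competence, will be collected before rollout. If not, report those outcomes descriptively too.

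The cost is mainly edits to Table 4 and the text, since the survey already runs in every cluster at every wave. Whether the questionnaire needs a new answer category cannot be judged, because it is not shown. The drawback is that the survey relies on respondents' recall of when symptoms began and treatment was given; this should be stated as a limitation.
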